### Subgroup analysis

To evaluate differential results concerning the predictive value of the PET analysis between male and female patients a separate analysis for both groups will be performed.

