#### **3.2 Recruitment**

It is planned to recruit a maximum of 40 patients over a 15 months period.

Patients will be recruited after screening only if all inclusion criteria are met, no exclusion criteria are met and written informed consent has been obtained. No difference in recruitment concerning gender will be applied. According to the distribution of NSCLC more male than female study participants are expected.

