## Analyses of primary endpoints

1. The prognostic value/accuracy of FDG-/FLT-PET regarding non-progression in NSCLC patients treated with erlotinib will be evaluated by ROC analysis (area under the ROC curve, AUC);  $H_0: AUC_{\text{FDG/FLT PET}} \leq 0.5$ ,  $H_A: AUC_{\text{FDG/FLT PET}} > 0.5$  (intersection-union test at one-sided level 2.5% – *primary objective*).

2. The statistical association of EGFR respectively KRAS mutational status, EGFR positivity and clinical response in NSCLC patients treated with erlotinib will be evaluated by Fisher's exact test (at one-sided level 2.5%; strong type 1 error control is maintained if analysis of item 1 was significant – *secondary objective*).

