## Sample size calculation

Assumptions:

- (1) 10% responder, 60% progressers; thus 40% non-progressers
- (2) Primary variable is the 'area under the ROC curve (AUC,  $\vartheta$ )', (PET-values of non-progressers > progressers)
- (3) Variability in the PET-results of non-progressers is greater than that of progressers
- (4) Type-I-error 0.05; type-II-error 0.20
- (5) True accuracy (AUC) is at least 0.70 (alternative hypothesis; some common diagnostic tests have an AUC greater than 0.70 [1; p29])

Sample size calculation:

| AUC ( $\vartheta$ ) | # Non-progressers | # progressers | # Total   |
|---------------------|-------------------|---------------|-----------|
| 0.70                | 26                | 38            | 64        |
| 0.75         | 16         | 24     | 40 |
| 0.80                | 11                | 16            | 27        |

Note: The sample size was calculated using formulae (6.3) and (6.6) in [Zhou et al., 2002; p199, 201].

Thus, assuming  $\vartheta_1 = 0.75$ , 40 patients are needed to reject the null hypothesis  $H_0: \vartheta = 0.5$  in favour of the alternative  $H_1: \vartheta \neq 0.5$ . The sample size will be sufficient to yield a 95% confidence interval for  $\vartheta$  with width  $2 \times 0.17 = 0.34$ .

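### The subgroup plan asks whether PET accuracy differs between men and women but fixes only separate analyses by sex, which neither estimate nor test that difference

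*Protocol*

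**What the plan says.** The Subgroup analysis paragraph in section 7.3 is a single sentence. Its aim is comparative: "To evaluate differential results concerning the predictive value of the PET analysis between male and female patients". Its method is not: "a separate analysis for both groups will be performed". The protocol contains no between-sex AUC difference, no confidence interval for one, no interaction test and no remark on power by sex.

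Four other places bear on the point.

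- Section 3.2 (Recruitment) caps enrolment: "It is planned to recruit a maximum of 40 patients over a 15 months period". It gives the sex balance only in words: "According to the distribution of NSCLC more male than female study participants are expected".
- The sample size calculation in section 7.3 assumes "10% responder, 60% progressers; thus 40% non-progressers" and "Type-I-error 0.05; type-II-error 0.20". It sizes the trial for one pooled AUC of 0.75 against 0.5, with 16 non-progressers and 24 progressers.
- Section 7.2 (Analyses of primary endpoints) gives the only test of an AUC, against 0.5 in the whole sample: "intersection-union test at one-sided level 2.5" per cent.
- Section 7.4 fixes the nonparametric DeLong method for ROC analysis.

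**The concern.** A question about a difference needs an estimate of the difference. Two AUCs reported side by side, each with its own interval or its own test against 0.5, leave the reader to judge by eye whether men and women differ. The most common way of doing that is to note that one result is significant and the other is not.

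The trial has 80% power for the pooled AUC at 0.75. Split into two groups of about 20, or less evenly, each sex has roughly even odds or worse of reaching significance. Discordant results are then ordinary even when PET works equally well in both. Because more men are expected, the discordance will more often look as if PET works in men but not in women. At stake is an unsupported statement about sex in the trial report; the primary conclusion is not affected.

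**Working it through.** **Inputs.** From the protocol: 40 patients, 40% non-progressers (16 to 24), planning AUC 0.75 with 0.70 and 0.80 as alternatives, type I error 0.05, power 80%, DeLong analysis. The one-sided 2.5% level of section 7.2 has the same critical value, 1.96, as a two-sided 5% test. Assumptions: 10 to 20 women among the 40 (the protocol gives no figure), the same progression rate and the same true AUC in both sexes.

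**Step 1: reproduce the plan's own figure.** Take the binormal variance function V(A) = 0.0099 · exp(−a²/2) · [(5a² + 8) + (a² + 8)/R], with a = 1.414 · z(A) and R = 24/16 = 1.5.

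- V(0.5) = 0.0099 × (8 + 8/1.5) = 0.1320
- V(0.75), with a = 0.954, = 0.1161
- Non-progressers needed = (1.96√0.1320 + 0.842√0.1161)² / 0.25² = 15.97; total = 2.5 × 15.97 = 39.9, against 40 stated
- The same formula gives 63.5 and 26.9 for AUC 0.70 and 0.80, against 64 and 27 stated
- Half-width of the 95% interval = 1.96√(0.1161/16) = 0.167, against 0.17 stated

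The function matches the plan, so it can be applied within each sex.

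**Step 2: power within each sex at AUC 0.75.** With n non-progressers in a sex, power = Φ[(0.25√n − 1.96√0.1320)/√0.1161]. The chance that exactly one sex is significant is pM(1 − pW) + pW(1 − pM).

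| Men : women | Power, men | Power, women | Exactly one significant |
|---|---|---|---|
| 50 : 50 | 0.494 | 0.494 | 50.0% |
| 60 : 40 | 0.573 | 0.408 | 51.3% |
| 70 : 30 | 0.643 | 0.315 | 55.3% |
| 75 : 25 | 0.674 | 0.267 | 58.1% |

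The even split already gives 50%. Low power in both halves drives the result; imbalance adds a little and sets the direction.

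**Step 3: check by simulation of DeLong tests at AUC 0.75** (20,000 trials per row).

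| Women (non-progressers / progressers) | Exactly one significant | Men only | Women only |
|---|---|---|---|
| 16 (6/10) | 50.5% | 32.3% | 17.7% |
| 13 (5/8) | 52.5% | 38.8% | 13.7% |
| 10 (4/6) | 54.6% | 45.3% | 10.2% |

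**Step 4: vary the assumptions.**

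- Over AUC 0.70 to 0.80 the rate is 45-59% by formula and about 39-55% by simulation.
- At AUC 0.90 it falls to about 6-21%, or up to 25% if the non-progressers' SD is 1.5 times that of the progressers.
- If each sex had to pass on both tracers, as in the intersection-union test, per-sex power at AUC 0.75 and an even split lies between 0.494² = 0.244 (independent tracers) and 0.494 (fully correlated). The rate is then between 2 × 0.244 × 0.756 = 37% and 50%.

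**Step 5: what a direct comparison could show.** At AUC 0.75, the standard error of the difference = √(0.1161/nM + 0.1161/nW), where n counts non-progressers. The detectable difference is (1.96 + 0.84) × SE.

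| Men : women | nM, nW | SE | 95% half-width | Detectable with 80% power |
|---|---|---|---|---|
| 50 : 50 | 8, 8 | 0.170 | 0.33 | 0.48 |
| 70 : 30 | 11.2, 4.8 | 0.186 | 0.36 | 0.52 |
| 75 : 25 | 12, 4 | 0.197 | 0.39 | 0.55 |

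Power for a true difference of 0.20 is about 19-22% at splits from 50:50 to 70:30.

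**Step 6: does the obvious interval work?** Adding the two DeLong variances and forming a Wald interval gives about 89% coverage with 10 women and 92% with 13, instead of 95%. With 4 non-progressing women, the women's observed AUC is exactly 1 in about 7% of trials and its DeLong variance is then zero. A simple bootstrap fails in the same case, because every resample of perfectly separated data also has AUC 1.

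**The case against.** Three objections have force.

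First, a reader might infer that the plan will itself produce a false sex contrast in about half of trials. The protocol does not support that. The Subgroup analysis paragraph sets no test or level within each sex and no rule that turns one significant and one non-significant result into a difference. The percentages above describe what happens if the results are read that way, at the planned accuracy.

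Second, a reader might infer that the planned analysis can never answer its question. That is also too strong. The two AUCs and their DeLong variances are exactly what a comparison needs, and nothing forbids taking the difference. A statistical analysis plan, if there is one, may do so. What stands is that the protocol states a comparative aim and names a method that stops short of it, so a plan that follows the text carries the gap forward.

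Third, it is tempting to blame the smaller number of women. The even-split result shows otherwise.

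On weight, the trial is described as therapeutic exploratory, sex appears in none of the 14 secondary objectives, and the subgroup sits under Further analyses. That argument stands in full and sets the severity.

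**Conclusion.** The aim and the method of the subgroup analysis do not match, and the mismatch is in the text. Its practical size is conditional. If the two results are compared by significance, equal accuracy would give a discordant pair in roughly 40-55% of trials at AUC 0.70-0.80 for a single tracer, about 37-50% at AUC 0.75 if both tracers must pass, and much less often at AUC 0.90. These figures rest on an assumed 10-20 women among 40, equal progression rates by sex and one-sided 2.5% tests within each sex, none of which the protocol fixes. The tilt towards men only follows from the expectation in section 3.2 that "more male than female study participants are expected".

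Severity is minor. The primary analysis and the listed objectives are untouched; only a statement about sex is at risk.

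**What to change.** Amend the Subgroup analysis paragraph in section 7.3 as follows.

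1. Keep the AUC in men and the AUC in women, for FDG and for FLT.
2. For each tracer, add the AUC in men minus the AUC in women with a 95% confidence interval. Use a small-sample method that does not collapse when one AUC equals 1, such as a score-type interval, or a logit-transformed interval with a stated adjustment for that case. Neither the plain summed-DeLong Wald interval nor a simple bootstrap should be relied on alone.
3. Label the comparison exploratory. Base any statement about a sex difference on that interval, and not on which sex reached significance.
4. State the limits in advance: a half-width of about 0.33-0.36 (0.39 if only 10 women enrol), so that only a difference of about 0.5, the gap between a perfect test and a useless one, is detectable with 80% power.

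The cost is one extra analysis per tracer, with no new patients, visits or data. The interval will be wide, which is an accurate account of what 40 patients can show about sex.

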## 7.4 Data analysis

Raw data of PET will be analyzed by two experienced nuclear physicians in consensus by visual control and semiquantitative (Standardized Uptake Value, SUV) methods using the MPI-tool with knowledge of the CT-findings. Results of the diagnostic procedures will be documented in the CRF on the same day or up to 3 days thereafter latest. Tomograms will

be analyzed in all three planes (coronar, sagital, transversal). Data will be correlated with computed tomography. Data will be stored for direct comparison in the follow-up.

Raw data of CT will be analyzed by two experienced radiologists in consensus according to the RECIST criteria (Therasse *et al.*, 2000) with knowledge of the FDG-PET and FLT-PET. Results of the diagnostic procedures will be documented in the CRF on the same day or up to 3 days thereafter latest.

To assure data quality, an external review of imaging findings will be performed after enrollment of the last patient.

Statistical analysis will be performed by [name]. The ROC analysis will be performed nonparametrically according to (DeLong *et al.*, 1988).

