## 2 AIM OF TRIAL

Based on the survival benefit demonstrated in patients with relapsed NSCLC (Shepherd et al., 2005) as well as on its favourable toxicity profile compared to chemotherapy the EGFR-TKI erlotinib represents an attractive candidate to be included also in protocols for the first line treatment of NSCLC. Accordingly, preliminary data from phase II trials show promising response rates for erlotinib treatment in the first line setting (Giaccone, 2005). In parallel, in the near future further targeted drugs will be available for NSCLC treatment. For instance, the addition of the anti-VEGF monoclonal antibody bevacizumab has recently shown to prolong survival when added to standard chemotherapy as first line treatment of NSCLC. Thus, in order to optimize the choice and the sequence of new drugs in NSCLC treatment, an early identification of patients with no clinical benefit, i.e. patients with progressive disease under treatment, is desirable. In the ERLOPET trial, we aim at establishing PET analysis as a tool for early identification of NSCLC patients with no clinical benefit from monotherapy with erlotinib as first line treatment. A pre-treatment computed tomography (CT) scan will be performed for evaluation of the patients' individual tumor burden. FDG- and FLT-PET scans will be performed between d -10 and d1 (but prior to therapy) for identification of pre-treatment PET status. Between d7 and d14, FDG- and FLT-PET scans will be performed for the early identification of erlotinib non responders. The imaging procedures will be performed at different days, i. e. one procedure per day. After six weeks of treatment, final response evaluation will be performed using CT, FDG- and FLT-PET scans. These results will be correlated to the mutational status of the EGFR - and the KRAS gene and the expression of EGFR in pretreatment samples.

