##### **Secondary Objectives**

1. To identify PET characteristics for progressive disease following erlotinib treatment (changes in SUV during treatment)
2. To identify PET characteristics for response to erlotinib (changes in SUV during treatment)
3. To identify PET characteristics for stable disease following erlotinib treatment (changes in SUV during treatment)
4. To confirm the statistical association of EGFR mutational status and clinical response in NSCLC patients treated with erlotinib
5. To confirm the statistical association of KRAS mutational status and clinical resistance to treatment of NSCLC patients with erlotinib
6. To determine the discriminatory capability of FDG-/FLT- PET regarding EGFR and KRAS mutational status in NSCLC patients
7. To compare prognostic value of FDG-PET, FLT-PET and EGFR mutational status regarding clinical response in NSCLC patients treated with erlotinib
8. To identify EGFR and KRAS sequence characteristics for clinical response and stable disease following erlotinib treatment
9. To assess safety of Erlotinib
10. To determine response rates
11. To determine rates of stable diseases
12. To determine one-year FFTF
13. To determine one-year OS
14. To determine median overall survival time

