## Restaging procedures during and after erlotinib therapy

### Examinations

Since the primary objective of the proposed study is to evaluate the accuracy of FDG-/FLT-PET analysis for early prediction of erlotinib non-progression in patients with NSCLC, the FDG- and FLT-PET examinations will be performed in exactly defined periods before, during and after therapy (s. table below).

| Time point                             | Imaging of involved areas       |
|----------------------------------------|---------------------------------|
| Between d-10 and d1 (prior to therapy) | FDG-PET, FLT-PET, CT            |
| Day 1                                  | Start of therapy with erlotinib |
| Between d7 and d14                     | FDG-PET and FLT-PET             |
| Week 7                                 | FDG-PET, FDG-PET, CT            |

In week 7 the following clinical and laboratory analyses will be performed:

- Clinical examination including physical examination:
  - height, weight, vital signs, ECOG performance status
- Assessment of the neurological status
- Existing signs and symptoms
- Concomitant medication
- Laboratory assessment including:
  - blood count including differential count
  - serum electrolytes (Na, K, Ca),
  - liver function parameters (total bilirubin, ASAT, ALAT, AP,  $\gamma$ GT, LDH),
  - renal function parameters (creatinine, BUN, uric acid),
  - ESR
  - CYFRA 21-1, CEA

These examinations may not include examinations which might be necessary if chemotherapeutic treatment is planned for progressive disease (see 5.7.6).

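### Section 7.4 lets PET readers know the CT findings without limiting this to the baseline CT, so week-7 SUVs can be measured by readers who already know the RECIST outcome

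*Protocol*

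**What the plan says.** Section 7.4 of the Protocol sets the rules for reading the images.

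- PET is read by two nuclear physicians in consensus, visually and by "semiquantitative (Standardized Uptake Value, SUV) methods using the MPI-tool with knowledge of the CT-findings". No time point is attached to the CT.
- CT is read by two radiologists in consensus under RECIST, "with knowledge of the FDG-PET and FLT-PET".
- On timing of entry: "Results of the diagnostic procedures will be documented in the CRF on the same day or up to 3 days thereafter latest".
- For data quality, "an external review of imaging findings will be performed after enrollment of the last patient".

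The schedule comes from Section 2 and the imaging tables. On the early scan, Section 2 says: "Between d7 and d14, FDG- and FLT-PET scans will be performed for the early identification of erlotinib non responders". No CT is listed in that window. The week-7 row of the table reads "FDG-PET, FDG-PET, CT"; Section 2 and the dose table in Section 5.6 show that FLT-PET is also done then. On order, Section 2 says only: "The imaging procedures will be performed at different days, i. e. one procedure per day".

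The first secondary objective in Section 3.1 is "To identify PET characteristics for progressive disease following erlotinib treatment (changes in SUV during treatment"); objectives 2 and 3 are the same for response and for stable disease. Section 7.2 adds secondary ROC analyses for clinical failure, stable disease and response, with optimal cut-offs to be chosen.

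**The concern.** SUV is the test under study and the week-7 CT is the reference against which it is judged. If the people measuring SUV know the reference result, that knowledge can influence which lesion they measure and how they outline it. The protocol leaves them room: Section 5.6 and the PET appendix in Section 12.3 refer only to standard methods such as SUV, and do not name lesion selection, volume definition or type of SUV. Test and reference would then agree partly by construction. The PET characteristics of progression, stable disease and response would look sharper than they are, and cut-offs chosen from the same data would carry that forward.

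This is a different problem from CT being read with knowledge of PET, which Section 7.4 also prescribes. That rule affects the reference, whereas this one affects the marker. Masking the radiologists to PET would leave this clause as it stands.

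**Working it through.** The clause itself has no figure to reproduce. The check sets the timing rules side by side.

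**Early scan (day 7 to 14).**
- Latest scan is day 14. Latest entry is day 14 + 3 = day 17.
- Treatment weeks 1 to 6 are days 1 to 42 (Section 5.9), so week 7 starts on day 43.
- Gap from latest entry to earliest week-7 CT is 43 − 17 = 26 days, with no CT scheduled in between.

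If the entry rule is kept, the only scheduled CT that these readers can know is the baseline CT. The first reading of the early scan is protected.

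**Week 7.** There are three procedures (FDG-PET, FLT-PET, CT), one per day, in open order. Take three consecutive days, 1 to 3, as an illustration, with CT entry allowed from the day of the scan.

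| CT on | CT result can be entered from | Latest SUV entry for the two PET scans | Can CT be known before SUV entry? |
|---|---|---|---|
| day 1 | day 1 | days 5 and 6 | yes, both scans |
| day 2 | day 2 | days 4 and 6 | yes, both scans |
| day 3 | day 3 | days 4 and 5 | yes, both scans |

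So even when PET is scanned first, the three-day window lets the CT result come before SUV entry. Protection would need either prompt entry before the CT result, or more than three days between the last PET and the CT. The protocol requires neither. The two reading rules are also circular (PET knowing CT, CT knowing PET), so they do not settle which is read first.

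**What a drift would do (illustration only).** Assume normal SUV measures with equal unit variance in the two outcome groups, and a reading drift of *s* SD in the expected direction. Then

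AUC = Φ((d + s)/√2), with d = √2 · Φ⁻¹(true AUC).

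- True AUC 0.50: d = 0. For s = 0.1, 0.2, 0.3 the argument is 0.071, 0.141, 0.212, giving AUC 0.528, 0.556, 0.584.
- True AUC 0.75: d/√2 = 0.674. The argument becomes 0.745, 0.816, 0.887, giving AUC 0.772, 0.793, 0.812.

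The drift has no source in the documents. I give no error rates: Section 7.2 sets no significance level for these secondary ROC comparisons, and the primary test, an intersection-union test at one-sided 2.5%, is not the affected analysis.

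**Sample size.** Section 7.3 gives 16 + 24 = 40 for AUC 0.75. With the binormal variance V = 0.0099·exp(−A²/2)·[(5A² + 8) + (A² + 8)/k], A = 1.414·Φ⁻¹(AUC) and k = 1.5, V is 0.132 at AUC 0.50 and 0.116 at 0.75. Then n = (1.96·√0.132 + 0.842·√0.116)²/0.25² ≈ 15.97 non-progressers, and 1.5 × 15.97 = 23.95 progressers, total 39.9. The plan's figure reproduces. No input depends on who sees which CT, so the fix leaves N at 40.

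**The case against.** Four points can be made on the other side.

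1. *Unmasking is possible, not certain.* A reader might infer that week-7 SUVs are always measured with the outcome known. The documents do not support that. Scan order is open, and where PET is scanned and entered first only an earlier CT exists. This stands, and the point is limited to what the rule permits.

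2. *Objectives 1 to 3 may not use week-7 SUVs.* Change during treatment is equally met by the protected change from baseline to day 7 to 14. The first hypothesis in Section 7.1 concerns early examinations, and Section 7.3 links response to SUV reduction on days 8 and 9. This also stands. The concern applies only where week-7 values are used, but the wording of Section 3.1 allows that use and the scans are scheduled.

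3. *The primary AUC.* A reader might infer that the external review carries outcome knowledge into the primary analysis. It takes place when most week-7 outcomes will exist, and no masking is stated. But the protocol does not say that the review re-measures SUV, or that its values replace those in the CRF. The primary analysis would be exposed only if both happened.

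4. *PET readers need CT for anatomical localisation, and Section 2 uses CT and PET together for the final response evaluation.* The baseline CT gives localisation, although less well once anatomy has changed. Joint reading need not come before SUV entry.

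The trial is also labelled exploratory and these objectives are secondary. That limits the consequence but does not make the clause sound.

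**Conclusion.** The concern holds in a limited form. Section 7.4 tells PET readers to know the CT findings without restricting which CT, and the week-7 timing allows that to be the outcome CT. Any analysis using week-7 SUV change is open to bias towards a stronger link between PET and outcome. The size cannot be derived from the documents. Under an assumed drift of 0.1 to 0.3 SD with equal-variance normal data, AUC rises by 0.03 to 0.08 from a true 0.50 and by 0.02 to 0.06 from a true 0.75.

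The primary analysis is not shown to be affected, because the early SUVs must be recorded at least 26 days before the earliest week-7 CT. That conclusion assumes the three-day rule is kept and the originally entered values are the ones analysed.

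**What to change.** In Section 7.4:

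- Replace the open reference to CT in the PET reading rule by a statement that PET readers know the baseline CT only.
- Require week-7 SUVs to be entered and locked before the week-7 CT or RECIST result is disclosed to the PET readers. Joint reading of CT and PET for patient care can follow once the SUVs are locked.
- State that the primary analysis uses the day 7 to 14 SUVs as originally entered.
- State that any external re-measurement of PET is masked to the week-7 CT and to outcome.

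I would not add a requirement to measure week-7 uptake in volumes fixed at baseline. Such volumes miss new lesions, which are one route to progression. If mean SUV is used, they also take in background around a shrunken lesion, which creates its own link with outcome.

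The cost is wording and reading order, with the same readers and scans and N unchanged at 40. The one downside is that week-7 PET localisation relies on the baseline CT until the SUVs are entered.

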## Therapeutic procedure after 6 weeks of erlotinib therapy

Only patients with documented (clinical examination, CT, PET) tumor control under erlotinib therapy (CR, PR or, at least, SD in the restaging procedures in week 7) will continue erlotinib therapy until progression of disease. In all patients with documented progress after 6 weeks of therapy erlotinib therapy will be stopped. Further treatment in these patients depends on overall performance state and declared intention of the patient. If the patient and the principal investigator or one of the co-investigators agree upon chemotherapeutic treatment, this treatment will be offered to the patient in the Department I of Internal Medicine, University Clinic Cologne.

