### **Evaluation of target lesions**

- \* Complete Response (CR): Disappearance of all target lesions
- \* Partial Response (PR): At least a 30% decrease in the sum of the longest diameter (LD) of target lesions, taking as reference the baseline sum LD
- \* Progressive Disease (PD): At least a 20% increase in the sum of the LD of target lesions, taking as reference the smallest sum LD recorded since the treatment started or the appearance of one or more new lesions
- \* Stable Disease (SD): Neither sufficient shrinkage to qualify for PR nor sufficient increase to qualify for PD, taking as reference the smallest sum LD since the treatment started
- \* Non-progression: CR + PR + SD but not PD

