## 7.3 Further analyses

### Subsequent analyses

### Expected results

Based on the results of clinical trials with erlotinib in NSCLC patients in Western Europe and the US, we expect about 10% of patients with response (CR, PR) to treatment with erlotinib, about 30% with stable disease and about 60% with progressive disease. Furthermore, we expect about 90% of patients with mutated EGFR responding to therapy. KRAS mutations and EGFR mutations are expected to be nearly exclusive.

Based on published PET data, especially from patients with GIST treated with imatinib, we expect a nearly 100% association of clinical response (CR, PR in CT after 6 weeks of treatment) and reduction in SUV (PET analyses on days 8,9).

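### The CT/RECIST reading that defines progression for the primary ROC analysis is made with knowledge of the PET under test, so the AUC is at risk of upward bias

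*Protocol*

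**What the plan says.** All references are to the protocol.

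- **Reference standard.** Section 7.1 (Evaluation of target lesions) sets the two classes by RECIST: "Non-progression: CR + PR + SD but not PD". Section 7.3 (Expected results) ties response to CT: "CR, PR in CT after 6 weeks of treatment".
- **Who reads it, and how.** Section 7.4: "Raw data of CT will be analyzed by two experienced radiologists in consensus according to the RECIST criteria", and this is done "with knowledge of the FDG-PET and FLT-PET". The clause names both tracers and excludes no scan, so the day 7–14 scans are covered.
- **Index test.** The same section has PET read "using the MPI-tool with knowledge of the CT-findings".
- **Week-7 evaluation elsewhere.** Section 2 says "final response evaluation will be performed using CT, FDG- and FLT-PET scans". Section 5.9 (Therapeutic procedure after 6 weeks) refers to "Only patients with documented (clinical examination, CT, PET) tumor control under erlotinib therapy".
- **Second look.** Section 7.4 adds that "an external review of imaging findings will be performed after enrollment of the last patient". It does not say that this review is masked to PET, or that it supplies the class used in the ROC analysis.
- **Primary test.** Section 7.2: AUC above 0.5, intersection-union test, one-sided 2.5%, for FDG-/FLT-PET.

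**The concern.** In an accuracy study the reference classification should be made without sight of the test being evaluated. Here the readers who decide between SD and PD know the predictor. RECIST fixes the arithmetic of diameters, but the appendix in section 12.3 leaves room for judgement: any new lesion means PD, progression of non-target lesions is a matter of opinion, and target lesions are chosen for their suitability. These judgements fall on the PD versus non-PD boundary, which is the split used in the ROC curve. A doubtful call settled in the direction of the PET adds agreement that is not prediction.

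If this happens, the estimated AUC mixes predictive accuracy with reader influence. No analysis of the recorded data can separate the two afterwards; only a masked re-read could.

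**Working it through.** **1. The plan's own figure.** With A = 1.414·z(AUC) and R = 24/16 = 1.5, the binormal variance function is V = 0.0099·exp(−A²/2)·[(5A²+8) + (A²+8)/R].

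- AUC 0.50: A = 0, so V₀ = 0.0099 × (8 + 5.333) = 0.132.
- AUC 0.75: A = 0.954, so V₁ = 0.116.
- n = [1.96·√0.132 + 0.842·√0.116]² / 0.25² = 15.97, so 16 non-progressers and 24 progressers, 40 in all.
- 95% CI half-width: 1.96·√(0.116/16) = 0.167 (stated 0.17). Power at 16/24 is 80.1%.

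The stated sample size reproduces. It presupposes a class assigned independently of PET.

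**2. What swayed calls do to one useless tracer.** Let a share w of week-7 calls follow the early PET ranking (top 40% called non-progression) and the rest follow true status. The documents do not give w; it is an assumption. With a true AUC of 0.50:

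- a patient from the top 40% outranks a random patient with probability 0.6 + 0.4 × 0.5 = 0.80;
- a random patient outranks one from the bottom 60% with probability 0.4 + 0.6 × 0.5 = 0.70;
- expected AUC = w² + w(1−w)(0.80 + 0.70) + 0.5(1−w)² = 0.50 + 0.5w.

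About 2 × 0.4 × 0.6 = 48% of swayed calls would differ from the true class, so w = 10% (4 of 40 calls) means about two patients reclassified.

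The rejection rates come from simulation (16/24 patients, normal PET values, DeLong test, one-sided 2.5%):

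| Share w | AUC read, true 0.50 | Rejection, true 0.50 | AUC read, true 0.70 |
|---|---|---|---|
| 0% | 0.50 | about 3% | 0.70 |
| 5% | 0.525 | about 6% | – |
| 10% | 0.55 | about 9% | 0.73 |
| 20% | 0.60 | about 20% | 0.76 |

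The 3% in the first row is the small-sample behaviour of the DeLong test and is not part of the point.

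**3. If week-7 PET, not early PET, sways the reader.** Assume a correlation of 0.3 to 0.7 between week-7 and early PET. A useless tracer then reads about 0.51–0.53 with 4–6% rejection at w = 10%, and about 0.53–0.57 with 6–12% at w = 20%.

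**4. If both tracers must be significant.** Take both tracers as useless, calls following early FDG, and tracer correlations of 0 to 0.7. Joint rejection runs from under 0.5% to about 3% at w = 10%, and from about 1% or less to about 8% at w = 20%.

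**5. The passages side by side.** Sections 7.1 and 7.3 make the response category a matter of size on CT. Section 2 evaluates final response with CT and both tracers. Section 5.9 documents week-7 CR, PR or SD by clinical examination, CT and PET. No text says which of these feeds the ROC analysis.

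**The case against.** **The endpoint is RECIST, and RECIST contains no PET criterion.** This is correct, and it narrows the reader's discretion without removing it. A reader might infer from sections 2 and 5.9 that PET is built into the endpoint. The text does not establish that. Section 2 is a narrative of aims, and section 5.9 governs who continues erlotinib. Against sections 7.1 and 7.3 they are an inconsistency to be reconciled.

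**The figures in step 2 are a worst case.** They describe a single tracer with early PET deciding the call. The planned intersection-union test, as usually understood, needs both tracers, and step 4 shows that joint rejection can then stay near or below 2.5% at w = 10%. This stands, with a limit: if one tracer truly predicts, the other's per-tracer rate becomes relevant again, and the AUC estimate for the tracer that sways the reader is inflated however the test is built.

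**The early PET values are protected.** Results are documented within three days, so day 7–14 values should be fixed well before the week-7 CT. This protects the index test and does nothing for the reference standard.

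**There is an external review.** It would cure the problem only if stated to be masked to PET and to supply the primary classification. Its stated purpose is data quality.

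**Conclusion.** The point holds as a risk built into the protocol. The reference standard for the primary AUC is read with knowledge of the index test by explicit rule, and the text is inconsistent on whether PET enters the week-7 response category. The expected direction of bias is upward, because PET-informed calls agree with PET more often than independent calls do.

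A reader might go further and conclude that the AUC is certainly inflated, or that the 2.5% level certainly fails. The documents do not support that. They give neither the share of swayed calls nor the correlation between scans or tracers, so every figure in steps 2 to 4 rests on assumed values. What can be said is that a few swayed calls are enough to matter for one tracer: at 20%, a true AUC of 0.70 reads 0.76, above the 0.75 on which the trial was sized. The sample size calculation itself is not in question.

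**What to change.** - **Section 7.4.** State that the RECIST response reading used in the primary analysis is made on CT, masked to all FDG- and FLT-PET images and reports, and that this reading alone defines progression in the ROC analysis. There are two ways to obtain it: the two radiologists record it before PET is disclosed to them, or the planned external review reads CT masked and supplies it.
- **Limit the masking to that reading.** Section 5.5 lets PET guide which areas CT covers, and this can stay.
- **Sections 2 and 5.9.** Reconcile them with sections 7.1 and 7.3 as to the study response category. This asks for no change to any treatment rule.

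**Cost.** Protocol and reading-instruction wording, with no added scan or patient, and N = 40 stands. Because treatment decisions at the same centre also look at PET, the local route needs a fixed order of recording; the external route avoids this. The downside is that PET cannot be used to resolve an equivocal lesion in the study reading. The change is best made before week-7 readings are recorded; after that, only a fully masked re-read restores independence.
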